### Statistical analysis

2.6

Statistical analyses will be implemented by SPSS 17.0 and Microsoft Excel 2007 software. Data will be represented as mean ± standard deviation. A *t* test will be performed to compare the changes in measures within groups. Statistical significance will be considered at *P* < .05.

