### Research object

2.1

We aim to explore the optimal depth of gastric tube placement in perioperative period for laryngeal cancer patients.

We aim to compare and analyze the differences in postoperative comfort and prognosis between the traditional gastric tube placement method (control group) and the modified lower esophageal gastric tube placement method (experimental group).

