### Study method

2.2

A total of 80 patients with laryngeal cancer in otolaryngology, head and neck surgery department of Deyang people's hospital from May 2020 to April 2022 will be selected and randomly divided into control group and experimental group according to the numerical table. Analysis for comfort and prognosis were performed by general comfort questionnaire (GCQ)^[4]^ and various index including height, body mass index, albumin value, electrolyte, wound healing, pharyngeal fistula. By statistical analysis, the effects of 2 different gastric tube placement depths on comfort and nutritional status of laryngeal cancer patients will be evaluated.

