### Measurement of outcomes

2.5

Tools to measure primary indicators include the following:

(1)The incidence of gastric complications.(2)In this study, visual simulation scale and GCQ developed by Kolaba,^[4]^ an American comfort nursing specialist, will be used to evaluate the comfort level of the 2 groups of patients, including pain, acid reflux, upper abdominal burning sensation, and hiccup.(3)Objective indexes such as height, body mass index, albumin value, electrolyte, wound healing, and pharyngeal fistula will be used to evaluate the prognosis of the 2 groups of patients.

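### Section 2.6 names only mean ± SD and a within-group t test, which does not fit gastric complications or pharyngeal fistula and does not compare the two groups on them

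*Protocol article*

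**What the plan says.** Section 2.6 (Statistical analysis) of the protocol article is four sentences long. Besides the software, it fixes three things:

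- The summary: "Data will be represented as mean ± standard deviation". Nothing limits this to continuous measures.
- The test: a t "test will be performed to compare the changes in measures within groups". No other test is named.
- The threshold: "Statistical significance will be considered at" P < .05, with no statement of one or two sides.

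Section 2.5 (Measurement of outcomes) opens its list of primary indicators with "The incidence of gastric complications". Its third item covers prognosis: "Objective indexes such as height, body mass index, albumin value, electrolyte, wound healing, and pharyngeal fistula".

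The aim in Section 2.1 (Research object) is to "compare and analyze the differences in postoperative comfort and prognosis between the traditional gastric tube placement method (control group") and the modified placement. Section 2.2 (Study method) gives "A total of 80 patients with laryngeal cancer", divided at random into two groups. It states no allocation ratio.

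**The concern.** An incidence is a proportion of patients, and a fistula is present or absent. Neither is naturally described by a mean and standard deviation, and neither has a meaningful change from before surgery. A t test of change within one arm asks whether events happened in that arm. The trial asks whether tube depth altered how often they happened.

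If the section were followed as written, the indicator listed first would carry a P value for each arm and no estimate of the difference between arms. The same would hold for fistula, an outcome that bears on safety. A result that is significant in one arm and not in the other could then be mistaken for an effect of depth.

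**Working it through.** The article gives no event rate, effect size or power calculation, so there is no figure of its own to reproduce. The calculation below is illustrative.

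**Inputs.** Total of 80 patients and P < .05, from the article. Assumed: 40 per arm, two-sided testing, each event scored 0 before surgery and 0 or 1 afterwards, and incidences from 5% to 20%.

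**1. What the stated test does to an event.** With x events among n = 40 and p = x/n, the mean change is p and its variance is n·p(1−p)/(n−1). The one-arm t statistic is therefore

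t = p / √[p(1−p)/(n−1)] = √[39·p/(1−p)], on 39 degrees of freedom.

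- x = 3: √(39 × 0.075/0.925) = 1.78, P = .083.
- x = 4: √(39 × 0.10/0.90) = 2.08, P = .044.

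Four or more events make an arm significant, whatever happens in the other arm.

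**2. Behaviour when depth has no effect.** Let π be the binomial probability of a significant result in one arm of 40. With the same true incidence in both arms, exactly one arm is significant with probability 2π(1−π).

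| Assumed incidence, both arms | π | Exactly one arm significant |
|---|---|---|
| 5% | 0.138 | 0.238 |
| 10% | 0.577 | 0.488 |
| 15% | 0.870 | 0.226 |
| 20% | 0.972 | 0.055 |

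At 20%, both arms are significant with probability 0.972² ≈ 0.945.

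**3. How much comes from the test being within groups.** If a between-group pooled t test on the 0/1 data is used instead, it gives the same decision as the uncorrected chi-square test in all 1681 possible 40/40 tables. With a 30/50 split the two differ in 2 of 1581 tables. The damage in step 2 therefore comes almost wholly from the within-group comparison, and little from applying a t test to binary data.

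**4. What mean ± SD adds.** For a 0/1 variable the SD is essentially √[p(1−p)]: 0.30 at 10% and 0.40 at 20%. The rate fixes it, so it tells the reader nothing beyond the percentage.

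**5. Choice of replacement test (40/40, assumed rates).** Over incidences of 5%, 10%, 20%, 30% and 50%, the type I error of chi-square runs from 0.043 to 0.059, and that of Fisher's exact test from 0.004 to 0.033. For 40% against 20%, power is 0.50 and 0.41 respectively. Using chi-square throughout, with Fisher only where expected counts are small, avoids giving up that power needlessly.

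**The case against.** The strongest defence is that a change in a measure suits quantities taken repeatedly, such as body mass index, albumin, electrolytes and comfort scores. On that reading the section assigns no test to the event outcomes, and a short article may leave such detail to a fuller document that is not shown. This has some force. However, the section is not silent about the summary: it fixes mean ± SD for data without qualification. The one test it names also does not serve the between-group aim for any outcome.

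Four stronger readings are tempting, and the article does not support them.

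- **That a t test on binary data is itself the invalid step.** Step 3 of the working shows otherwise for a between-group test at this size. If the wording about groups is only a slip for a comparison between them, what remains is mainly a reporting fault: means instead of counts and percentages, and no risk difference with an interval.
- **That wound healing is a yes/no outcome.** Section 2.5 gives no scale. It could be a grade or a time to healing.
- **That a non-significant fistula result will be presented as absence of harm.** The article plans no equivalence or no-harm claim.
- **That symptom scales need a rank-based test.** The article says nothing about how the scores are distributed.

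**Conclusion.** The point holds. As written, Section 2.6 gives the first-listed primary indicator and pharyngeal fistula neither a fitting summary nor a comparison between the randomised groups.

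The illustrative size, one-arm-only significance in about 49% of trials with no true difference, is the largest of the four incidences tabulated. It rests on an equal 10% incidence, a 40/40 split and events coded 0 at baseline, none of which the article states. At 5% and 15% the figure is 24% and 23%, and at 20% it is about 6%, because there both arms are nearly always significant. These numbers measure the within-group fault as it falls on event outcomes. They should not be counted again if that fault is raised separately.

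The correction is needed before analysis because it decides what can be concluded on the indicator listed first.

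**What to change.** Amend Section 2.6 to say the following:

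- Gastric complications and pharyngeal fistula are reported as n/N (%) by group. They are compared between groups with a chi-square test, or Fisher's exact test when expected counts are small (threshold fixed in advance), and the risk difference is given with its 95% CI.
- Mean ± SD and the t test apply to continuous measures only, and the t test compares the two groups.
- Wound healing is analysed by a method that matches its scale. If it is recorded as yes/no, it is handled as a proportion in the same way as fistula. Section 2.5 should state the scale.

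The cost is a few sentences and standard procedures in the software already named. Sample size, visits and procedures do not change, and the only added definition is the wound-healing scale.

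### The only stated test compares changes within each arm; the between-arm aim needs a named comparison, and for continuous measures it should adjust for the baseline value

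*Protocol article*

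**What the plan says.** Section 2.6 of the protocol article contains a single inferential statement: "A *t* test will be performed to compare the changes in measures", and its closing words place that comparison within groups. It adds a mean ± SD summary and a threshold: "Statistical significance will be considered at *P* < .05". No covariate, regression model or two-sample comparison is named.

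Section 2.1 (Research object) sets a between-arm aim: to "compare and analyze the differences in postoperative comfort and prognosis between the traditional gastric tube placement method (control group") and the modified lower-oesophageal placement. Section 2.2 (Study method) says that the effects of the two depths on comfort and nutritional status will be evaluated. It gives the sample as "A total of 80 patients with laryngeal cancer in otolaryngology, head and neck surgery department", to be "randomly divided into control group and experimental group according to the numerical table".

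Section 2.5 (Measurement of outcomes) lists the prognostic indexes: "Objective indexes such as height, body mass index, albumin value, electrolyte, wound healing, and pharyngeal fistula will be used to evaluate the prognosis" of the two groups. Body mass index, albumin and electrolytes are the continuous ones that can change over the study. No section gives the time of the baseline or follow-up measurement.

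**The concern.** There are two linked faults.

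- **The test does not answer the question.** A change tested inside each arm says whether that arm moved, not whether the arms differ. The randomisation is unused, and a significant result in one arm beside a non-significant one in the other can be misread as a treatment effect.
- **The obvious repair keeps an inefficiency.** An editor who corrects the wording would probably write a two-sample t test on the changes. That subtracts the whole baseline value (slope fixed at 1) instead of estimating how far the baseline predicts the later value. When the true slope is below 1 it over-corrects: precision is lost, and an arm that happens to start lower appears to improve more through regression to the mean.

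With 80 patients, the precision of the nutritional comparison is at stake, although the values needed to improve it are probably already being collected.

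**Working it through.** **Inputs from the article.** 80 patients (2.2), two randomised arms (2.2), significance level 0.05 (2.6).

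**Assumptions not in the article.** 1:1 allocation (40 per arm), two-sided test, no dropout, true between-arm difference of 0.5 SD, equal pre and post SDs (set to 1), and a pre-post correlation rho from 0.3 to 0.9. The article states no power or effect size, so it has no figure to reproduce.

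**Step 1: the test as written.** Suppose that both arms have the same true change, equal to 0.3 SD of the change, so there is no treatment effect. A paired t test with n = 40 has noncentrality 0.3 × √40 = 1.90 and power 0.457 in each arm. The chance that exactly one arm is significant is 2 × 0.457 × (1 − 0.457) = 0.496. Within-arm testing would therefore give discordant results about half the time with no difference between the arms.

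**Step 2: residual variance of the two between-arm analyses.**
- Change score: variance 2(1 − rho), 78 degrees of freedom.
- ANCOVA: variance 1 − rho², 77 degrees of freedom.
- Ratio of ANCOVA to change score: (1 − rho²) / [2(1 − rho)] = (1 + rho)/2, which is below 1 for any rho below 1.

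Without equal SDs, the change-score variance exceeds the ANCOVA variance by (SD_pre − rho × SD_post)². This is zero only when the true slope, rho × SD_post/SD_pre, equals 1.

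**Step 3: power.** Noncentrality is 0.5 / √(variance × 2/40), evaluated with the noncentral t. At rho 0.5 this is 0.5/√(1.00 × 0.05) = 2.24 for the change score and 0.5/√(0.75 × 0.05) = 2.58 for ANCOVA.

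| rho | Variance, change | Variance, ANCOVA | Ratio | Power, change | Power, ANCOVA |
|---|---|---|---|---|---|
| 0.3 | 1.40 | 0.91 | 0.65 | 46.3% | 63.9% |
| 0.5 | 1.00 | 0.75 | 0.75 | 59.8% | 72.2% |
| 0.7 | 0.60 | 0.51 | 0.85 | 81.4% | 87.1% |
| 0.8 | 0.40 | 0.36 | 0.90 | 93.7% | 95.7% |
| 0.9 | 0.20 | 0.19 | 0.95 | 99.9% | 99.9% |

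**Step 4: baseline imbalance.** The standard error of the baseline difference is √(2/40) = 0.224 SD. Given an imbalance, the change-score difference shifts by −(1 − rho) times that imbalance. For an imbalance of one standard error the shift is 0.7 × 0.224 = 0.16 SD at rho 0.3, 0.5 × 0.224 = 0.11 SD at rho 0.5 and 0.3 × 0.224 = 0.07 SD at rho 0.7, in favour of the arm that started lower if a rise is the good direction. Simulation gave slopes of −0.69, −0.50 and −0.30. The simulated mean of the estimator over all randomisations was within 0.002 SD of zero.

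**The case against.** **The power figures concern a test that the article does not state.** This is correct. As written the test is within groups, so the figures do not show what the stated plan loses. They show why a two-sample t test on changes would be an incomplete repair. The absence of a between-arm comparison is the larger fault, and baseline adjustment comes second.

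**A reader might infer that change scores bias the trial.** The documents do not support that. Allocation is random, so the between-arm difference in change is unbiased over randomisation. The shift in Step 4 is conditional on the imbalance that occurs, and the change-score standard error already reflects that variation. It is the same inefficiency seen from another side and should not be counted as a second loss.

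**A reader might single out albumin.** Section 2.5 gives it no priority: it is one of six items in the third of three sets of indicators. Of the other five, height is not a sensible outcome, and wound healing and fistula are not natural change scores.

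**The size is assumed.** This stands. If postoperative spread is larger than baseline spread, the slope can reach 1 and the gain disappears; at rho 0.7 that takes an SD ratio of 1/0.7 = 1.43. Body mass index may well have rho of 0.9 or more, where the gain is negligible anyway.

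**The baseline timing is inferred, and an article is condensed.** A change needs an earlier value, but the article does not say that it precedes the intervention. Lack of stated stratification or covariates would not by itself be a finding, since such details may stand in a fuller document. What remains is that the article does fix an analysis, and the analysis it fixes neither compares the arms nor uses the earlier value beyond subtraction.

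**Conclusion.** The point holds in a limited form. Section 2.6 commits to a within-arm t test on changes, which cannot deliver the between-arm comparison that section 2.1 sets as the aim. When that is corrected, the baseline value should enter as a covariate and not only by subtraction.

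The advantage of adjustment in residual variance does not depend on the assumed effect size, and it vanishes only where the true slope equals 1; the price is one degree of freedom. Its size depends wholly on assumptions. Under those listed above, the gain is about 18 percentage points of power at rho 0.3, 12 at rho 0.5, 6 at rho 0.7, 2 at rho 0.8 and none of note at 0.9. This is a worthwhile, nearly free improvement. It is not evidence that an unadjusted change-score comparison would be invalid.

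**What to change.** In section 2.6, for each continuous measure with a pre-intervention value (such as albumin, electrolytes and body mass index, but not height), replace the within-group t test with a linear model (ANCOVA). The outcome is the postoperative value; the covariates are treatment group and the patient's own baseline value. Report the adjusted between-group difference with its 95% CI. State when the baseline and postoperative values are taken.

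Suggested wording: *For each continuous measure recorded before the intervention, the postoperative value will be compared between the randomised groups by analysis of covariance, adjusting for that patient's baseline value; the adjusted difference and its 95% confidence interval will be reported.*

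The cost is that sentence, a note of the measurement times and one residual degree of freedom per model. SPSS 17.0, already named in 2.6, fits the model. No new data are needed where the baseline value is already taken to compute a change; where it is not, it would have to be recorded.

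### The one test named in section 2.6 compares changes within groups, which contradicts the between-group aim in section 2.1 and does not suit the event outcomes

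*Protocol article*

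**What the plan says.** **Aim (section 2.1, Research object).** The question is between groups: to "compare and analyze the differences in postoperative comfort and prognosis between the traditional gastric tube placement method (control group") and the modified lower-oesophageal placement in the experimental group.

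**Design (section 2.2, Study method).** "A total of 80 patients with laryngeal cancer" are to be "randomly divided into control group and experimental group according to the numerical table". The allocation ratio is not given. The same section adds: "By statistical analysis, the effects of 2 different gastric tube placement depths on comfort and nutritional status of laryngeal cancer patients will be evaluated". It names no test.

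**Outcomes (section 2.5).** Three items are listed as primary indicators. The first is an event rate: "The incidence of gastric complications". The second is comfort, by a visual scale and the general comfort questionnaire (GCQ). The third is a set of objective indexes: height, body mass index, albumin, electrolytes, wound healing and pharyngeal fistula.

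**Analysis (section 2.6).** Data are summarised as mean and standard deviation. The only test named is a t "test will be performed to compare the changes in measures within groups". "Statistical significance will be considered at" P < .05, with no statement of one- or two-sided.

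**The concern.** A test of change within one group asks whether that group's mean differs before and after. In this setting the change contains surgery, recovery and the passage of time as well as tube depth. The Introduction itself says that patients have a tracheotomy and recover slowly. Both arms share these influences, and randomisation removes them only when the arms are compared with each other. Two separate within-arm tests leave that comparison out.

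Two things are at stake if an analyst carries out 2.6 as printed:

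- The results would contain no estimate, interval or P value for the difference between placements, which is the stated aim.
- A reader left with two within-arm P values may compare them informally. A significant change in one arm and a non-significant change in the other is not a test of the difference between arms.

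The named test also fails to fit some outcomes. Gastric complications and pharyngeal fistula are events, with no evident value before tube placement from which to form a change, and a t test on a mean change is not a natural analysis for them.

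**Working it through.** **1. The passages side by side.**

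| Section | What it fixes | Between-group test named? |
|---|---|---|
| 2.1 | Aim: difference between the two placements | No |
| 2.2 | 80 patients randomised; effects of the two depths to be evaluated | No |
| 2.5 | Comfort and prognosis described for the two groups | No |
| 2.6 | t test of changes within groups, P < .05 | No |

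The aim is between groups and the only named test is within groups. This step needs no assumption, and the finding rests on it.

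**2. No figure to reproduce.** The article gives no effect size, standard deviation, event rate, power or derivation of the 80 patients. What follows is an illustration.

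**3. Inputs to the illustration.**

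- Total of 80: section 2.2.
- 40 per arm: assumed, because no ratio is stated.
- 5% level: section 2.6. Two-sided: assumed.
- True change, in units of the SD of the change: assumed, shown from 0 to 0.8, and the same in both arms (so tube depth has no effect).
- Decision rule, significant in exactly one arm: hypothetical, not in the article.

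**4. Formulas.** For a within-arm t test with n = 40, the critical value is t(0.975, 39) = 2.023 and the noncentrality is d × √40. The power w is the probability that a noncentral t with 39 degrees of freedom falls outside ±2.023. With independent arms, the chance that exactly one is significant is 2w(1 − w).

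**5. Results.**

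| Common true change d (SD) | d × √40 | Within-arm power w | Exactly one arm significant, 2w(1 − w) |
|---|---|---|---|
| 0 | 0 | 0.050 | 9.5% |
| 0.2 | 1.26 | 0.235 | 36% |
| 0.3 | 1.90 | 0.456 | 50% |
| 0.4 | 2.53 | 0.694 | 42% |
| 0.5 | 3.16 | 0.869 | 23% |
| 0.6 | 3.79 | 0.959 | 8% |
| 0.65 | 4.11 | 0.980 | 4% |
| 0.8 | 5.06 | 0.999 | 0.3% |

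Worked line at 0.4 SD: 2 × 0.694 × 0.306 = 0.425.

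The rate peaks near 50% at about 0.3 SD and drops below the nominal 5% by about 0.65 SD.

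**6. Large changes in both arms.** At 0.8 SD both arms are significant with probability 0.997. If the arms truly changed by 1.0 and 1.5 SD, both tests would be significant with probability above 0.999, and neither result would carry information about the 0.5 SD difference.

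**7. What a direct comparison offers.** A two-sample t test with 40 per arm (same assumptions, 78 degrees of freedom) has power of about 60% at a between-arm difference of 0.5 SD and 94% at 0.8 SD. By the normal approximation, 80% power is reached at √(2/40) × (1.960 + 0.842) = 0.63 SD. Here the SD is that of the analysed measure. A direct test keeps its 5% error rate whatever the common change.

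**The case against.** The strongest reply is that the between-group intent is plain. Sections 2.1, 2.2 and 2.5 and the Discussion all speak of two groups or two placement methods, and 2.6 is a short passage in a condensed article. Its sentence could be loose wording for comparing the changes of one group with those of the other. That is plausible, and it limits the point: the fault lies in the analysis sentence, not in the design. It does not remove the point, because 2.6 is not silent. It names a test, and the test named does not answer the question in 2.1. Even under the generous reading, a t test of changes would not fit gastric complications or fistula.

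Three stronger readings are tempting, and the document does not support them:

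- **That the trial cannot say anything about which placement is better.** Randomised data on both arms will exist, and the aim is stated. A corrected sentence recovers the comparison.
- **That the false-positive rate will be far above 5%.** The percentages above belong to a decision rule that appears nowhere in the article. Even under that rule the rate depends on the common change: it is high between 0.2 and 0.5 SD and below 5% from about 0.65 SD. The article gives no change or SD, and large shared changes after surgery are quite possible.
- **That analysis of covariance (ANCOVA) is required.** A two-sample t test would also resolve the contradiction. The article does not state that comfort is measured at baseline, and tube-related symptoms may have no useful value before placement.

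**Conclusion.** The point holds as a contradiction within the document. Section 2.6 names one inferential test, of changes within groups, while section 2.1 sets a between-group aim and no section supplies a between-group test. Carried out literally, 2.6 does not test the difference between tube depths and does not suit the event outcomes, including the first-listed primary indicator. This is a misstatement rather than detail left to another document, and it should be corrected before analysis.

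The size of any resulting error cannot be read from the article. The range from 0.3% to about 50% for significance in exactly one arm is conditional on 40 per arm, a two-sided 5% level, equal true change in both arms and an unstated decision rule. The verdict does not depend on it.

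**What to change.** Replace the test sentence in section 2.6 with wording such as:

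> The primary analysis compares the randomised groups. Continuous outcomes (symptom scale, GCQ, BMI, albumin, electrolytes) are compared between groups by ANCOVA of the postoperative value adjusted for baseline where one exists, otherwise by a two-sample t test, and reported as a mean difference with 95% CI. Binary outcomes (gastric complications, pharyngeal fistula, and wound healing if recorded as yes/no) are compared between groups by chi-square or Fisher exact test, with a risk difference and 95% CI. Within-group changes are descriptive only, without P values.

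The cost is a change of wording. It needs no further patients, data or software, since these are standard procedures in the SPSS package already named. If the sponsor did mean a comparison of changes between groups, saying so resolves the contradiction for the continuous outcomes, but the clause for binary outcomes is still needed.
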